## Abstract

**Background:**

Evidence regarding the treatment of displaced, extraarticular lateral clavicle fractures is scarce. No study has shown clinically significant differences between surgical and nonsurgical treatment, but the sample sizes have been small, as it has been difficult to include enough patients with this relatively uncommon fracture type.

**Purpose:**

This study aims to compare outcomes after surgical and nonsurgical treatment for displaced lateral clavicle fractures.

**Methods:**

This is a pragmatic, noninferiority, preference-tolerant, randomized controlled trial (RCT). A total of 100 patients between the ages of 18 and 65 with displaced lateral clavicle fractures will be randomly allocated on a 1:1 ratio to surgical or nonsurgical treatment with the option of early crossover after 6 weeks. An observational cohort will comprise patients not willing to be randomized. This is a multicenter Scandinavian RCT including hospitals in Sweden, Norway, Denmark, and Finland. The primary outcome is the Disabilities of the Arm, Shoulder and Hand (DASH) score at 1 year. Follow-up points will be 6 weeks, 3 months, 6 months, and 1 year. The secondary outcomes are the DASH score, the EQ-5D-5L score, the University of California, Los Angeles (UCLA) activity score, the Nottingham Clavicle Score (NCS), a visual analog scale (VAS) for pain, and anchor questions in the form of the Patient Global Impression of Change (PGIC) collected at all timepoints during the study. All complications, radiographic healing, and return to work will be reported.

**Discussion:**

The optimal treatment for displaced Neer type II and V lateral clavicle fractures remains a topic of debate. This RCT may provide a better understanding of the differences in outcomes of nonsurgical and surgical treatment while reflecting real-world clinical practice and guiding the development of a treatment algorithm for the orthopedic community.

**Trial registration:**

ClinicalTrials.gov NCT06981065. Registered on 19 May 2025. https://clinicaltrials.gov/study/NCT06981065?term=Scandilac&rank=1

**Supplementary Information:**

The online version contains supplementary material available at 10.1186/s13063-026-09844-8.

## Background and rationale

Clavicle fractures constitute 3–4% of all fractures in adults [1, 2]. Midshaft fractures are most common (65–82%) followed by lateral (12–30%) and finally medial (2–6%) fractures. Most lateral clavicle fractures (LCFs) are extraarticular. There is a typical bimodal pattern consisting of young males and elderly women. The injury pattern is often sports-related (dominated by cycling) or traffic accidents in the young or simple falls in the elderly [3–6]. LCFs are often classified according to Neer, modified by Craig, where types II and V are unstable and equivalent to a coracoclavicular (CC) disruption (see Supplementary material 1, S1) [7, 8].

High-quality trials comparing treatment of displaced extraarticular lateral clavicle fractures (LCFs) are scarce. No published RCT has included enough patients to provide sufficient statistical power to detect clinically meaningful differences.

The desire to restore the anatomy and to avoid nonunion have been the main reasons for surgical treatment of displaced LCFs. Nonunion rate after nonsurgical treatment has been reported as high as 33% [7–10]. Surgical treatment of an LCF commonly consists of plate fixation (anatomical locking plate or hook plate) with or without CC fixation [11–17]. Complications after surgical treatment are relatively common, particularly when using hook plates, which can cause subacromial erosion, osteolysis, and rotator cuff injury [18–21]. Hook plate removal is advocated after about 3 months, and many regard this secondary procedure as part of the treatment algorithm [22–24].

However, several systematic reviews and meta-analyses have reported no difference in patient-reported outcome measures (PROMs) between surgical and nonsurgical treatment, even in cases with radiological nonunion [10, 25, 26]. Two RCTs have attempted to provide evidence in this regard, but both were underpowered [27].

The aim of this study is to determine if nonsurgical treatment is noninferior to surgical treatment of Neer type II and V displaced LCFs.

## Methods: participants, interventions, comparisons, and outcomes

### Objectives

To compare PROMs of patients allocated to surgical or nonsurgical treatment of displaced Neer type II and V LCFs, including early identification and treatment of potential symptomatic delayed union.

### Trial design

A pragmatic, multicenter, randomized, outcome assessor-blinded, noninferiority trial. The ScanDiLaC protocol conforms with the Standard Protocol Items: Recommendations for Interventional Trials (SPIRIT) [28]. Patients not randomized and treated according to preference will be offered inclusion in an observational cohort.

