### Outcomes

#### Data collection

All data apart from PROMs (which are automatically sent out to participants via e-mail) is entered directly into REDCap© by a trial worker directly involved in the trial.

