#### Primary outcome measure

The DASH score at 1 year.

For the upper extremity, the DASH score is the most used general PROM and it is validated and reliable for use in a multitude of pathologies in the upper extremity [36–38]. It has been validated for use in several upper extremity disorders [39] and has been cross-culturally adapted into Swedish, Danish, Norwegian, and Finnish populations [40].

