#### Secondary outcome measures

Upper extremity function and symptoms will be measured by the DASH at all timepoints.NCS at all timepoints.General health status questionnaire measured by the EQ-5D-5L.Shoulder pain will be assessed by an 11-point VAS, where patients are asked to assess their overall pain in the arm from 0 to 10 in a day.Healing will be assessed via routine radiographs by the participating centers at 1 year. Radiographic union is defined as cortical bridging between the medial and lateral fragments. Symptomatic nonunion is defined as a lack of radiographic union in combination with clinical signs of nonunion (movement at the fracture site, persisting pain) [41]. Radiographic nonunion without symptoms will be recorded but not considered an adverse event.Malunion of some degree is expected with nonsurgically treated clavicles and is therefore characterized by being symptomatic or not [42].Return to work collected from participants at all timepoints.Anchor questions in the form of the PGIC at all timepoints presented with 7 response options and analyzed as a 7-point Likert scale.Adverse events (AEs) after treatment will be recorded and include (see Table 2).

**Table 2 Tab2:** Safety outcomes

Adverse event		
Surgical		Non-surgical
Deep infection (FRI)	Vascular injury or injury to brachial plexus	Symptomatic nonunion**
Superficial infection	Fixation failure	ACJ arthritis
Hardware irritation	Nonunion	Impingement
Supraclavicular nerve injury*	Scar or wound issues	
Serious adverse events (SAEs)—defined by the US Food and Drug Administration (FDA) [43] as any untoward medical occurrence that results in death, is life-threatening, results in hospitalization, significant disability, or permanent damage, or requires intervention to prevent impairment or damage. Major adverse cardiovascular events (MACEs) is a type of SAE that is defined as acute myocardial failure (AMI), stroke, cardiovascular death, heart failure (HF), and unstable angina		

^*^Prevalence varies greatly between studies [44, 45]

^**^Asymptomatic nonunion is not counted as an adverse event for the purpose of this study but will be recorded

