### Blinding

As this is a surgical vs nonsurgical treatment trial, it is not feasible to blind patients or surgeons to the treatment allocation. The statistical analysis will be performed by a blinded biostatistician not connected to the project apart from the statistical analysis.

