## Data management and safety

The PROM questionnaires will be sent out by e-mail, but physical copies will be available. A researcher will check for completeness in REDCap and review them for missing data. If data are missing, the worker, without interference from the medical staff, will assist the participants in completing the questionnaires. Clinician-assessed data are fed directly into REDCap by a physician active in the study at each follow-up visit. Study-related information is stored in REDCap, which is protected with secure firewalls and requires authentication for access. Access will be restricted to trial workers currently working on the trial, and their access will be restricted to data entry. The principal investigator (PI) will keep a list of all persons with access. Data will be pseudonymized prior to analysis and publication.

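### The assessor-blinding label in the trial design statement is wrong for the primary outcome, which unblinded patients rate themselves

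*Protocol article*

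**What the plan says.** The Trial design section of the protocol article introduces the study as "A pragmatic, multicenter, randomized, outcome assessor-blinded, noninferiority trial". The Blinding section says that "it is not feasible to blind patients or surgeons to the treatment allocation", and then names one blinded role: "The statistical analysis will be performed by a blinded biostatistician not connected to the project apart from the statistical analysis".

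The primary outcome is given as "The DASH score at 1 year". The same section classes the instrument as patient-reported ("the DASH score is the most used general PROM"), and the Data collection section describes the route: "All data apart from PROMs (which are automatically sent out to participants via e-mail) is entered directly into REDCap".

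For outcomes that are not patient-reported, Data management and safety says: "Clinician-assessed data are fed directly into REDCap by a physician active in the study at each follow-up visit". Secondary outcome measures says: "Healing will be assessed via routine radiographs by the participating centers at 1 year". Central review of radiographs appears only under Participants, where its purpose is to check eligibility.

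**The concern.** The assessor of an outcome is whoever makes the rating. For a questionnaire that the patient answers, this is the patient. A trial in which patients know their treatment and the deciding outcome is a patient questionnaire cannot be assessor-blinded for that outcome.

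What is at stake is what the trial can claim. Readers and authors of evidence syntheses use this label to judge protection against detection bias. In an open comparison of surgery with no surgery, patients' expectations can move self-rated function in either direction. A shift against nonsurgical treatment makes noninferiority harder to show. A shift in its favor makes a false noninferiority claim more likely. The label suggests a safeguard that the primary comparison does not have.

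**Working it through.** **Step 1. Who rates each outcome, and is that person described as blinded?**

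| Outcome | Rated or recorded by | Blinding stated |
|---|---|---|
| DASH at 1 year (primary) | patient, by e-mailed questionnaire | no; Blinding section says patients cannot be blinded |
| NCS, EQ-5D-5L, pain VAS, PGIC, UCLA activity score | patient | as above |
| Return to work | collected from the patient | as above |
| Radiographic healing | participating centers | none stated |
| Clinical signs, complications | study physician at follow-up visits | none stated |
| Statistical analysis | biostatistician | blinded, but this is not outcome assessment |

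For the first three rows the Trial design and Blinding sections contradict each other. For healing and complications the article describes no blinded assessor. Two further places suggest that follow-up staff know the arm: the Crossover section offers crossover at the 6-week visit only in the nonsurgical arm, and Table 2 lists different adverse events for each arm. That is indirect evidence, not a statement.

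**Step 2. Does the point disturb the planned sample size?** Inputs from the Sample size section: margin 10.4, SD 14.3, one-sided alpha 0.025, power 90%. The true difference is taken as 0.

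- n per arm = 2 × (1.960 + 1.282)² × 14.3² / 10.4² = 39.7, rounded up to 40, so 80 in total.
- With 20% attrition: 80 / 0.80 = 100.

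Both planned figures reproduce. The noncentral t gives 89.5% power at 40 per arm and 90.2% at 41, so 80 is within tolerance. Blinding enters none of these inputs.

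**Step 3. How sensitive is the primary comparison to unblinded rating?** The documents give no reporting-bias figure, so the shift b is an assumption and is shown as a range in both directions.

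- SE = 14.3 × √(2/40) = 3.20, on 78 degrees of freedom.
- Shift against nonsurgical treatment, true difference 0: power uses noncentrality (10.4 − b) / 3.20.
- Shift favoring nonsurgical treatment, true difference equal to the margin: type I error uses noncentrality b / 3.20.

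| Assumed shift b (DASH points) | Power, shift against nonsurgical | One-sided type I error, shift favoring nonsurgical |
|---|---|---|
| 0 | 89.5% | 2.5% |
| 1 | 82.7% | 4.9% |
| 2 | 73.7% | 9.0% |
| 3 | 62.8% | 15.1% |
| 5 | 38.5% | 33.9% |

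These values show why it matters to know whether DASH is blinded. They do not measure the wording error, because they are the same whatever the trial is called.

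**The case against.** The strongest defense has four parts.

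- **The article is open about blinding.** Anyone who reads the Blinding section learns that patients and surgeons are not blinded. This limits the harm, but it also confirms the contradiction: the design statement is the line most likely to be carried into summaries, and the Blinding section does not support it.
- **Assessor masking may be described in the full protocol.** For healing and complications this stands. A reader might infer that no outcome in the trial has a blinded assessor, because clinicians would see a scar or an implant. The article does not say this. It does not identify the recording physician as the treating surgeon or state that this person knows the allocation. A patient who crosses over may also have a scar and an implant, so these show treatment received rather than randomized arm. For DASH the defense fails, because no further document can turn an unblinded patient into a blinded assessor.
- **Medical staff are kept out of questionnaire completion.** Data management and safety has a worker help with missing answers without clinical staff interfering. That is a partial safeguard against clinician influence. It is not blinding, since the patient still gives the answer.
- **Blinding patients is not feasible here.** Agreed. The open design is not the error. It also follows that the power and type I error figures describe an unavoidable feature of the trial and are not a cost of the label.

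**Conclusion.** The point holds as a contradiction between the Trial design section and the Blinding section. The label is wrong for DASH at 1 year and for the other patient-reported outcomes, which include most of the secondary ones. For healing and complications the supportable statement is narrower: no blinded assessor is described.

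Three stronger readings are not supported. That assessor blinding exists nowhere in the trial goes beyond the text for clinician-assessed outcomes. That the label costs the trial power, for example a fall from 89.5% to 73.7%, attributes to wording what comes from an assumed 2-point shift under open treatment. That the label is repeated elsewhere cannot be shown: the article's abstract does not carry it, and the registry record is not at hand.

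Sample size, analysis and conduct are unaffected. The correction is still worth making, because it changes what the trial can claim about detection bias on the outcome that decides noninferiority. The conclusion rests on DASH being self-completed and patients knowing their treatment, both of which the article states.

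**What to change.** Reconcile the Trial design and Blinding sections. Describe the trial as open-label with blinded statistical analysis, and acknowledge that the primary DASH comparison is unblinded. If a blinded assessor does exist for a specific outcome, such as radiographic healing, name the outcome, say how the assessor is blinded, and restrict the label to that outcome. If reporting bias is discussed quantitatively, present it as an assumed range in both directions.

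The cost is a change of wording and a slightly less favorable design description. Nothing in the sample size, the analysis model or the follow-up schedule has to change.

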### Study setting

Sites from Sweden, Denmark, Norway, and Finland were recruited. They span from level I to III trauma centers. The Trial Steering Committee (TSC) consists of representatives from all participating countries.

The initial recruiting hospitals are summarized in Supplementary material 2 (S2) (with the expectation that the list will grow as interest and awareness of the study increases).

### Participants

The trial population will consist of adults aged 18–65 years presenting to one of the participating centers with Neer type II or V displaced LCF, without contraindications to either of the treatment arms (Table 1). Participants must provide informed consent and be able to complete follow-up including questionnaires in the Scandinavian languages or English.

**Table 1 Tab1:** Inclusion and exclusion criteria of the ScanDiLaC trial

Inclusion criteria
Displaced Neer type II or V LCFs—fractures extending from the midshaft of the clavicle can be included if the majority of the fracture is located in the lateral part
Patient aged 18–65 years
Exclusion criteria
Same-time injury in the upper extremity estimated to affect the primary outcome
Polytrauma*
Pathological fracture
Open fracture
Neurovascular injury
Not treatable within 21 days of injury
Contraindications to anesthesia or surgery due to comorbidities
Unable to give informed consent (such as dementia, unwillingness to participate, mental disabilities)
Inability to complete follow-up, such as not being able to fill out questionnaires in Swedish, Danish, Norwegian, Finnish, or English)

^*^As defined by the New Berlin definition [29], see Supplementary material 3 (S3)

The lateral part of the clavicle extends from the medial border of the coracoid process to the acromioclavicular joint. Displacement varies greatly with body position, muscle tension, and radiographic view. Because of this, a pragmatic approach will be taken, meaning that fractures with any displacement can be included, and it will be up to each center to determine if a fracture is displaced and eligible for inclusion. Radiographs will be uploaded in the data collection software to allow central review for validity of inclusion.

#### Recruitment

Patients admitted to the emergency department at any of the trial sites will be clinically examined, and radiographs will be obtained to confirm the diagnosis. If the inclusion criteria are met and no obvious exclusion criterion is present, the patient will be given the study information which contains all relevant information pertaining to the study, a simple sling to rest the injured arm, and then be scheduled for an outpatient appointment with a physician active in the study recruitment within 10 days. At this visit, the patient is informed about the study and given time to ask questions about study procedures. Upon documented informed consent in the data collection software, randomization is performed.

#### Randomization

Research Electronic Data Capture (REDCap©) is a computerized database software hosted by Uppsala University [30]. It will be used to perform block randomization through an irreversibly random allocation sequence with selected block sizes of 2 and 4, stratified by site. Patients will be allocated in a 1:1 ratio between surgical and nonsurgical treatment. The trial worker who includes the patient will then acquire the allocated treatment from REDCap and initiate the treatment, either by scheduling the patient for surgery or commencing nonsurgical treatment according to the study protocol. The trial flowchart for the ScanDiLaC study is seen below (Fig. 1).

**Fig. 1 Fig1:**
[figure not shown]
Trial flowchart for the ScanDiLaC study. dLCF, displaced lateral clavicle fracture

### Interventions and comparison

The interventions below are reported according to the TIDieR checklist [31]. The common recommended physical therapy protocol for both groups (see Supplementary material 4 and 5, S4, S5) is based on the Swedish physiotherapy program Axelina®, which is a standardized protocol for treating various conditions in the shoulder girdle [32].

#### Nonsurgical treatment

Appropriate nonsurgical treatment will be performed according to a standardized common physiotherapy protocol recommended for both interventions, with an initial period of immobilization consisting of a simple sling followed by structured physiotherapy. The sling is worn until pain resolves and when careful range of motion exercises can commence under the supervision of a licensed physiotherapist. The physiotherapy consists of home exercises combined with face-to-face visits with the physiotherapist if needed. The frequency and timing will be a shared decision between the patient and the physiotherapist. Adherence to physical therapy will be controlled by the physician during follow-up visits and recorded in REDCap.

#### Surgical treatment

The method of fixation can include plates (anatomic locking plate or hook plate) and screws ± CC fixation or CC fixation alone [33]. The plate will be applied via a supraclavicular approach to the lateral clavicle with screws in the proximal and distal fragments following basic principles of fracture fixation. The exact technique, type of plate, and CC fixation will be the treating surgeon’s choice and will be recorded.

Postoperatively, the arm will be placed in a sling, and unloaded exercises will commence from day one. The sling is initially used for comfort and can often be discarded approximately 1 to 2 weeks postoperatively. The type of sling and continued postoperative exercise regimen and physiotherapy will continue according to the recommended rehabilitation protocol, as described in the nonsurgical treatment above.

The level of experience of the operating surgeon will not be defined, but they must be familiar and experienced with the fixation method and material they are using. Each participating center will take responsibility to ensure that this is followed.

#### Crossover

In line with recent evidence regarding midshaft clavicle fractures and the development of symptomatic nonunion [34, 35], we intend to include the option of crossover to surgical treatment at the 6-week follow-up visit in the nonsurgical study arm if there are signs of the patient being at risk for symptomatic nonunion (severe persisting pain, no healing on radiographs) and if the patient requests surgery. Time from decision to surgery should be within 3 weeks.

### Outcomes

#### Data collection

All data apart from PROMs (which are automatically sent out to participants via e-mail) is entered directly into REDCap© by a trial worker directly involved in the trial.

#### Outcome timepoints

Outcome measures will be obtained at the following timepoints: preinjury, baseline, 6 weeks, 3 months, 6 months, 1 year, 2 years, and 5 years. Study follow-up visits for the ScanDiLaC study is seen below (Fig. 2).

**Fig. 2 Fig2:**
[figure not shown]
Study follow-up visits. DASH, Disabilities of the Arm, Shoulder and Hand; NCS, Nottingham Clavicle Score; EQ-5D-5L, European Quality of Life—5 Dimensions, 5 Levels; VAS, visual analog scale; UCLA, University of California, Los Angeles; PGIC, Patient Global Impression of Change; X1, preinjury scores; X2, primary outcome

